Previous studies of radiation-free treatment (RFT) in stage I–IIA HL patients with classic Hodgkin lymphoma without B symptoms and extra-nodal disease (eHL), the RAPID, H10, HD16 clinical trials, failed to demonstrate non-inferiority within margins of 7–10% [6,7,8]. However, in those trials, approximately 60–70% of patients were cured with chemotherapy alone. On the other hand, a small but non-negligible percentage of patients ultimately experience disease relapse after CMT. Therefore, an unmet need exists for a better stratification of eHL to tailor therapy according to individual disease risk, with the goal of preserving efficacy while minimizing RT-related TRM and with a better prognostic patient stratification to single out the small patient subset failing CMT. In these studies, cure with chemotherapy alone was achieved mainly in patients with negative interim positron emission tomography (PET) after the second chemotherapy cycle (PET-2). Conversely, approximately 25% of patients with a positive PET-2 (H10 trial) did not respond to standard CMT [7]. To date, PET-2 is regarded the strongest predictor of treatment failure not only in advanced disease but also in early-stage disease [7]. Classical bulky disease is a well-known unfavorable prognostic factor. Consistently, in a retrospective reappraisal of predictive factors for treatment outcome in the RAPID trial, a large nodal mass with the largest diameter ≥ 5 cm (LNM), measured on baseline contrast-enhanced computed tomography (CT), emerged as a strong predictor of treatment failure (HR 3.78, 95% CI 1.59–9.02; *p* = 0.003) [9]. The total metabolic tumor volume (TMTV) calculated on the PET/CT performed at baseline also proved to be of prognostic value in eHL, although different methods for TMTV computing have been proposed and different cut-off values have been adopted [10]. In patients enrolled in the standard arm of the H10 trial, a TMTV value > 147 mL indicated a risk of treatment failure 21% higher compared to that of patients with a lower value. [5]. However, in 129 non-bulky stage I–IIA patients from the French cohort of the H10 study, who matched the inclusion criteria of the RAFTING trial, a much lower value of 84 mL proved to be the most accurate threshold for predicting favorable treatment outcome. Patients with a TMTV value > 84 mL had a treatment failure rate of 44%, compared with 4% among patients with a lower value (unpublished observation, [name], personal communication, 2019). Finally, the H10 study showed that about 12.6% of RFT patients relapsed, and among them, 73% exclusively in the initially involved regions [7].

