### 2.5. Sample Size

The sample size calculation was based on the following assumptions: the anticipated 3-year progression-free survival (PFS) rate for stage I–IIA non-bulky eHL patients with a negative PET-2, treated with CMT, is 94% [6]; the expected 3-year PFS for PET-2-negative patients with similar clinical characteristics, treated with chemotherapy alone comprising two to four courses of chemotherapy, ranges between 87% and 93%, as reported in three prospective and one retrospective clinical trials, despite variations in patient characteristics and treatment intensity [6,7,8,28].

The expected 3-year PFS for PET-2-negative patients with TMTV < 84 mL treated with chemotherapy alone is anticipated to be at least 90%. In this context, a one-sample non-inferiority design was employed to calculate the sample size required to test whether the proportion of low-risk eHL patients, treated with chemotherapy alone, alive and disease-free at 3 years, is non-inferior to that of patients treated with CMT. For the non-inferiority assessment of the primary endpoint, we assumed an expected true response proportion of 90%. The non-inferiority historical reference value was set at 95%, reflecting the historical outcome of CMT reported in trials such as RAPID and H10, with an absolute non-inferiority margin of 10 percentage points; thus, non-inferiority would be concluded if the response proportion in the study population exceeds 85%.

To define the sample size of patients to be enrolled, we used a one-sided type I error of 0.20 and type II error of 0.20 (80% power). “The one-sided α of 0.20 was prespecified because the study was designed as an exploratory Phase 2 screening trial, in which minimizing false-negative findings was prioritized over controlling false-positive findings, consistent with the recommendations of Rubinstein et al.” [29].

A total of 102 low-risk (defined by a low MTV and a negative PET-2) eHL patients should be enrolled to exclude a difference between the true proportion and the comparison value of at least 10%. Considering an expected 75% of patients with a negative PET-2 and low TMTV, and a drop-off rate of 15%, 160 patients had to be enrolled in the trial.

In the exploratory phase 2 setting, a one-sided α = 0.20 was chosen because the potential harm of a false negative result (failing to recognize an effective treatment) is considered more significant than that of a false positive result (proceeding to confirmatory testing) [29].

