### 2.6. Statistical Methods Used to Compare Groups for Primary and Secondary Outcomes

The primary efficacy endpoint is 3-year progression-free survival (PFS) in the LR group, which will be evaluated for non-inferiority relative to a prespecified historical control rate. The PFS in the LR group is defined as the time from LR patient registration to the first occurrence of disease progression (limited or extended relapse) or death for any reason. The PFS distribution will be estimated using the Kaplan–Meier product-limit method, and the standard error of the 3-year survival estimate will be computed using Greenwood’s formula. For the primary hypothesis, a one-sided 80% confidence interval (CI) for the 3-year PFS rate will be constructed. Non-inferiority will be concluded if the lower bound of this one-sided 80% CI exceeds 85%, corresponding to a one-sided type I error rate (alpha) of 0.20.

The first secondary endpoint is also used for LR patients only. The 3-year freedom from second treatment failure (FF2TF) is calculated for LR who have limited relapse only and are rescued according to the protocol. It is measured from registration to the date of second relapse (during or after RT followed by nivolumab) (extended relapse) or death for any reason. FF2TF will be estimated using the Kaplan–Meier method, and the 3-year FF2TF estimate will be reported with a two-sided 95% confidence interval (CI) derived using Greenwood’s formula.

The second secondary efficacy endpoint is the 3-year PFS in the HR cohort, defined as the time from HR patient registration to the first occurrence of disease progression (extended relapse) or death for any reason. The 3-year PFS estimate will be obtained from the Kaplan–Meier curve, with a two-sided 95% CI calculated using Greenwood’s formula.

Both secondary assessments will allow us to calculate 3-year event-free survival (EFS) across the entire study cohort. The EFS is defined as the time from patient registration to the failure of the planned study treatment, which varies by study groups and includes only extended relapses or death for any reason. This is considered one of the most important study aims, reflecting the efficacy of a flexible-intensity and personalized treatment offered to different eHL prognostic groups. The 3-year EFS estimate will be obtained from the Kaplan–Meier curve, with a two-sided 95% CI calculated using Greenwood’s formula.

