The third secondary endpoint is 3-year overall survival (OS) of the entire cohort of patients enrolled into the study, defined as time from patient registration to death for any reason. The OS will be estimated using the Kaplan–Meier method, with a two-sided 95% CI based on Greenwood’s standard error.

As this is a single-arm evaluation, analyses of the secondary endpoints will be descriptive and will report point estimates with corresponding measures of precision, without formal hypothesis testing against a concurrent comparator. The summary of the study outcomes is presented in Table 1.

Finally, the diagnostic performance of cfDNA for detection of an impending relapse during follow-up in LR group patients will be summarized using overall accuracy, sensitivity, specificity, negative predictive value, and positive predictive value. Each metric will be presented as a point estimate with a two-sided 95% CI computed using the Clopper–Pearson exact method.

As an intention-to-treat (ITT) approach is preferred for phase III randomized clinical trials and a per protocol (PP) approach is preferred for equivalence and non-inferiority trials, a PP analysis will be preferred for assessing the primary study endpoint of treatment efficacy in LR patients, and an ITT approach will be used as secondary [30]. For all the other study endpoints in the RAFTING study, both an ITT and PP will be used.

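### The Greenwood 95% interval prescribed for 3-year FF2TF will rest on about 7 to 11 patients and has zero width if no rescued patient fails; OS shares the fault if deaths are very few

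*Protocol article*

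**What the plan says.** Section 2.6 of the protocol article bases every time-to-event estimate on Kaplan–Meier with Greenwood's formula.

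- **FF2TF.** The analysis is confined to low-risk patients who have a limited relapse and receive the in-protocol rescue (section 2.6 and Table 1). For it, "the 3-year FF2TF estimate will be reported with a two-sided 95% confidence interval (CI) derived using Greenwood’s formula".
- **OS.** The whole cohort is analysed, "with a two-sided 95% CI based on Greenwood’s standard error".
- **Primary PFS.** "the standard error of the 3-year survival estimate will be computed using Greenwood’s formula". The sentence fixes the standard error; the scale on which the limit is formed is not named.

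The cfDNA accuracy measures in the same section are given Clopper–Pearson exact intervals instead. No expected number of FF2TF patients, no expected FF2TF rate and no expected 3-year OS is given. The figures that allow the FF2TF group to be sized are in section 2.5 ("A total of 102 low-risk (defined by a low MTV and a negative PET-2) eHL patients should be enrolled", and a true proportion of 90%) and in the Introduction, where the H10 trial is reported to show that "about 12.6% of RFT patients relapsed, and among them, 73% exclusively in the initially involved regions".

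**The concern.** Greenwood's standard error is a large-sample quantity. It needs a reasonable number of events and an estimate that is not close to 0% or 100%. FF2TF is restricted to a subset that the plan's own assumptions make very small, and success of the rescue means few or no events. In that case the formula returns limits above 100% or, with no event, a standard error of exactly zero. OS over three years in favourable early-stage disease may meet the same problem from the other side: many patients but possibly very few deaths.

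At stake is how the rescue strategy will be read. Section 2.6 makes the secondary endpoints descriptive, so the interval is all the inference there is. FF2TF is the only listed endpoint that isolates rescue with radiotherapy plus nivolumab, which section 1 names as a study aim. An interval of 100% to 100% from some eight patients would tell readers that the result is certain.

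**Working it through.** **1. The plan's own sample size.** Inputs from section 2.5: true proportion 0.90, bound 0.85, one-sided type I error 0.20, power 0.80 (z = 0.8416 for each).

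n = 0.90 × 0.10 × (0.8416 + 0.8416)² / 0.05² = 101.999, so 102 as stated. Total: 102 / (0.75 × 0.85) = 160, as stated. Before drop-off, 160 × 0.75 = 120 low-risk patients.

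**2. Size of the FF2TF group.** Low-risk patients × relapse proportion × share in the original regions:

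| Low-risk patients | Relapse 10% (design PFS 90%) | Relapse 12.6% (H10 figure) |
|---|---|---|
| 102 | 102 × 0.10 × 0.73 = 7.4 | 102 × 0.126 × 0.73 = 9.4 |
| 120 | 120 × 0.10 × 0.73 = 8.8 | 120 × 0.126 × 0.73 = 11.0 |

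Eight patients is used below as a representative size.

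**3. What the interval looks like with 8 patients.** Without censoring before 3 years, Kaplan–Meier with Greenwood reduces to a proportion p with standard error √(p(1−p)/n).

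- 8 of 8 event-free: the standard error is 0, so the interval is 100% to 100% on any scale. Exact lower limit: 0.025^(1/8) = 63.1%.
- 7 of 8 event-free: √(0.875 × 0.125 / 8) = 0.117, and 0.875 ± 1.96 × 0.117 gives 64.6% to 110.4%. Exact: 47.3% to 99.7%.

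**4. Actual coverage of the nominal 95% interval with 8 patients.** The binomial probabilities of all outcomes whose interval contains the true value are summed. For a true 90%, the untransformed intervals for 5, 6 and 7 successes contain it and no others do: 0.033 + 0.149 + 0.383 = 0.565. The document gives no true FF2TF, so a range is shown.

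| True FF2TF (assumed) | Untransformed | Log(-log) | Clopper–Pearson | Chance of no failure |
|---|---|---|---|---|
| 50% | 93% | 96% | 99% | 0.4% |
| 60% | 84% | 93% | 98% | 2% |
| 70% | 93% | 88% | 99% | 6% |
| 80% | 82% | 78% | 99% | 17% |
| 85% | 71% | 71% | 98% | 27% |
| 90% | 57% | 53% | 99% | 43% |

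The last column is p⁸, for example 0.90⁸ = 0.43. The fault does not depend on exactly eight patients: at a true 85%, untransformed coverage is 53% with 5 patients and 82% with 11.

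**5. OS with 160 patients.** With no deaths the Greenwood interval is 100% to 100%; the exact lower limit is 0.025^(1/160) = 97.7%. With 2 deaths it is 97.0% to 100.5%, against exact limits of 95.6% to 99.8%.

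| True 3-year OS (assumed) | Untransformed | Log(-log) | Clopper–Pearson |
|---|---|---|---|
| 90% | 95.5% | 95% | 97% |
| 97% | 86% | 97% | 97% |
| 98% | 83% | 92% | 98% |
| 99% | 80% | 78% | 98% |

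**6. Primary rule, for comparison.** With 102 patients and no censoring, 90 event-free gives a lower one-sided 80% limit of 0.8555 untransformed and 0.8525 on the log(-log) scale; 89 gives 0.8448 and 0.8418. Both scales therefore pass from 90 of 102, with the same type I error (0.223) and power (0.78).

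**The case against.** The strongest reply has four parts.

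- **The endpoints are descriptive.** No hypothesis is tested on FF2TF or OS, so no decision turns on these intervals. This stands and limits the consequence to reporting.
- **The assumed rates are favourable to the criticism.** The only rescue figures in the document are about 30%, for radiotherapy without nivolumab (sections 1 and 3). At a true 50% to 70% with 8 patients, the untransformed interval covers 84% to 93% and a zero-width interval is unlikely (0.4% to 6%). This also stands: the size of the fault depends on how well the rescue works, and it is worst when the rescue works well.
- **OS near 100% is not in the plan.** Section 3 gives only survival of around 90% in general terms, and at 90% the Greenwood interval is sound. The OS part is therefore conditional.
- **The scale is analysis-plan detail.** This fails for FF2TF. Greenwood is written in as the method, and no scale repairs a zero standard error; log(-log) coverage is no better at 80% to 90%.

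A reader might go further and infer that Greenwood's formula also inflates the primary type I error from 0.20 to about 0.22, and that power should be restated as about 77%. The document does not support this. At the planned 102 without censoring, 0.223 comes from the discrete cut-off of 90 patients, which log(-log) shares. As the number of patients varies, the untransformed rule falls on both sides of 0.20 (0.187 at 120, for instance). An excess of about 0.02 appears only on averaging over sample sizes or under assumed censoring, and only if an untransformed limit is used, which section 2.6 does not specify. Nor do all intervals rest on Greenwood, since the cfDNA intervals are exact.

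**Conclusion.** The point holds for FF2TF, and conditionally for OS. The method named for FF2TF is unsuitable for the 7 to 11 patients that the document's own figures imply. With no second failure it yields an interval of no width where the exact one spans 63% to 100% (8 patients). With an assumed true rate of 80% to 90%, a nominal 95% interval covers 82% down to 57% untransformed, and 78% down to 53% on the log(-log) scale. For OS the shortfall (86% to 80% untransformed, at a true 97% to 99%) depends on an OS level that the plan does not state.

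The coverage figures assume complete 3-year follow-up. The group size assumes that the 73% share carries over to this trial's definition of limited relapse, which also admits up to three new nodal sites. Even if every relapse counted as limited, the group would be only 102 × 0.10 = 10 to 120 × 0.126 = 15 patients. The consequence is misleading precision in descriptive results; the primary test is not affected.

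**What to change.** Replace the Greenwood interval for FF2TF and for OS by an exact-type interval: Clopper–Pearson if every patient is followed to 3 years or to an event, otherwise a beta-product or likelihood-ratio interval for the Kaplan–Meier estimate. State in advance that FF2TF is expected to rest on about 8 patients, and report the number at risk and the number of events beside the estimate. The primary rule and its stated power need no change on this account.

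The cost is a few lines in the analysis plan, and section 2.6 already uses Clopper–Pearson for cfDNA. The article says follow-up is ongoing, so the change can still be made before the analysis. The price is wider reported intervals: Clopper–Pearson is conservative, covering about 98% to 99% with 8 patients.

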In summary, the planned treatment for LR groups 1a and 1b includes two or four chemotherapy cycles. In the case of limited relapse, INRT and nivolumab maintenance are given to both groups. In the HR group, the planned frontline treatment consists of a triple-modality regimen (four chemotherapy cycles followed by INRT and nivolumab). The extended relapse, defined as all other forms of disease relapse in the LR group or any relapse in the HR group, defines the failure of planned treatment and results in patient withdrawal from the study (Figure 2).

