### 2.4. Study Procedures

The recruitment period was planned from April 2021 to December 2023. Depending on risk stratification, patients undergo 18–49 visits, including the screening and the 12 follow-up visits (one every 3 months over the 36-month follow-up period).

At screening, the following data are collected: demographic and clinical characteristics; physical examination findings; disease-specific data (histological subtype, stage, number of involved nodal areas, extranodal involvement); patient breakdown according to mEORTC criteria; laboratory test results, Eastern Cooperative Oncology Group (ECOG) performance status; and functional test results, including pregnancy testing.

At treatment visits, the following data are collected: all changes in symptoms, physical examination, laboratory results; treatments administered; and adverse events. Pregnancy is verified at each treatment visit.

Collected information data during follow-up visits include date and extension of relapse in case of treatment failure; subsequent lymphoma treatment; secondary malignancies, cardio-vascular disease, and other organ toxicity; and survival.

Patients achieving complete metabolic response (CMR) on both PET-2 and end-of-treatment PET (EoT-PET) by blinded independent central review (see below) will undergo routine follow-up: clinical and laboratory evaluations every 3 months for the first 3 years, and additionally, a cfDNA assay (every 3 months during the first year, and every 6 months during the second year). PET imaging is performed only when indicated by clinical symptoms or laboratory abnormalities. If PET suggests HL relapse, a biopsy is strongly recommended to confirm the diagnosis of disease recurrence. Patients meeting criteria for limited relapse are included in group 2 and receive “delayed” INRT followed by nivolumab 240 mg every 14 days for 1 year.

Routine clinical data will be documented at study sites and entered into a secure, web-based electronic case report form (eCRF) system (The diCELLa eCRF Clinical Trials platform) (https://dicella.com/ecrf/ assessed on 14 August 2026). Documentation is sourced from routine medical records and verified for completeness through centralized and on-site monitoring by medical managers and clinical monitors. Imaging data and cfDNA are integrated with clinical data in the eCRF.

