The sample size calculation was based on the proportion of patients cured with RFT in previous prospective studies. Consequently, the primary endpoint of this phase 2 prospective, single-cohort clinical trial is the 3-year PFS in the low-risk group of patients treated with chemotherapy alone. The non-inferiority design provides a rigorous framework for determining whether radiation-free chemotherapy regimens can achieve efficacy comparable to conventional CMT within a 10% margin in this subgroup. The 10% non-inferiority margin was chosen based on statistical reasoning, clinical judgment, and the feasibility of implementing the study plan, balancing the risk of reduced disease control against the potential long-term benefit of omitting radiotherapy. A narrower margin, such as 5%, would have required a substantially larger sample size, approaching that of a confirmatory trial. Therefore, the present study is intended to exclude clearly unacceptable loss of efficacy and to inform the design of a subsequent phase 3 trial using a more stringent margin. We also referred to prior Hodgkin lymphoma trials that used a 7–10% non-inferiority margin to define clinically meaningful differences in efficacy (RAPID trial—7%, EORTC/LYSA/FIL H10—10%) [6,7].

Equally important is the main secondary endpoint, the 3-year EFS in all groups of patients, which will allow estimation of the proportion of patients who fail the planned treatment. Thus, the limited relapse in LR patients treated with delayed INRT and nivolumab is not considered as an event. The events defining the true failures of planned treatment include only extended relapse at any time or any relapse including limited relapse after completing the triple treatment.

The RAFTING trial is also the first prospective study to evaluate the role of cfDNA in eHL. By investigating cfDNA as a predictor of impending relapse, the trial aligns with the increasing interest in liquid biopsies as a non-invasive monitoring tool. This approach has the potential to enable earlier interventions in patients at risk of relapse and may ultimately improve long-term outcomes. Subsequent studies could refine cfDNA thresholds, assess cost-effectiveness, and evaluate the applicability of this approach in other lymphoma subsets.

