**Figure 2 biomedicines-14-01861-f002:**
[figure not shown]
Study treatment scheme. ABVD—doxorubicin, bleomycin, vinblastine, dacarbazine, Gy—Gray, INRT—involved node radiation therapy, mEORTC—modified EORTC criteria, PET-2—positron emission tomography after second chemotherapy cycle, TMTV—total metabolic tumor volume.

**Table 1 biomedicines-14-01861-t001:** The summary of study outcomes.

End-Point	Type	Group of Patients	Events
3-year progression-free survival (PFS) in low-risk group	Primary	Low-risk	Any progression (limited and extended relapse—whatever occurs first); death of any reason
3-year freedom from second treatment failure (FF2TF)	Secondary	Low-risk with limited relapse rescued in protocol (radiation therapy + nivolumab)	Progression during or after rescue treatment (extended relapse); death of any reason
3-year progression-free survival (PFS) in high-risk group	Secondary	High-risk	Extended relapse; death of any reason
3-year event-free survival (EFS)	Secondary	Entire cohort	Extended relapse (failure of planned per-protocol treatment—varies depending on stratification); death of any reason
3-year overall survival (OS)	Secondary	Entire cohort	Death of any reason

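### EFS is meant to measure failure of the treatment plan but counts only extended relapse and death, so persistent disease or unplanned lymphoma therapy leaves a patient event-free

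*Protocol article*

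**What the plan says.** Section 2.6 defines EFS for the whole cohort as the time until the planned treatment fails, "which varies by study groups and includes only extended relapses or death for any reason", and ranks it among the study's most important aims. The Discussion calls it the main secondary endpoint and closes the list again: "The events defining the true failures of planned treatment include only extended relapse at any time or any relapse including limited relapse" once triple treatment is complete. Table 1 gives the EFS events as "Extended relapse (failure of planned per-protocol treatment—varies depending on stratification); death of any reason". Extended relapse is itself a kind of relapse; Section 2.3 defines it as "all other forms of disease relapse in the LR group or any relapse in the HR group".

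The two PFS endpoints in Section 2.6 are built in the same way. HR PFS runs to the "first occurrence of disease progression (extended relapse) or death for any reason", and low-risk (LR) PFS to the "first occurrence of disease progression (limited or extended relapse) or death for any reason".

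Other parts of the article bear on this:

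- The Introduction reports that "approximately 25% of patients with a positive PET-2 (H10 trial) did not respond to standard CMT". The Discussion also names a subgroup that does not respond to combined-modality treatment (CMT).
- Section 2.4 sends the end-of-treatment PET (EoT-PET) to central review. It is read by Lugano or, after nivolumab, LYRIC criteria, with a consensus read for an indeterminate response. Subsequent lymphoma treatment is recorded.
- Section 2.4 describes routine follow-up for "Patients achieving complete metabolic response (CMR) on both PET-2 and end-of-treatment PET (EoT-PET) by blinded independent central review".
- Section 2.7 censors for loss to follow-up or withdrawal of consent.
- Section 2.5 words the primary question as the proportion of LR patients who are alive and free of disease at 3 years.

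**The concern.** The name and purpose of EFS are wider than its event list. A planned treatment can fail in at least two ways that are neither relapse nor death. First, the disease may never clear and still be present, without growth, on the final scan. Second, the patient may be moved to lymphoma therapy outside the planned pathway before any relapse is declared. Under the written list both patients stay event-free, and whatever later therapy achieves is credited to the study strategy. If such a patient withdraws consent, Section 2.7 censors the patient as non-informative, so again no event is recorded.

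The omission concerns the type of failure that the article itself gives as a reason for intensifying treatment. PET-2-positive patients are placed in the HR group because some of them did not respond to CMT. An endpoint that cannot register non-response cannot show whether triple therapy has dealt with it. The direction is one-sided: a failure left out of the count can only make EFS and HR PFS look better.

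**Working it through.** **Reproducing the plan's own figures (Section 2.5).** Inputs: expected rate 0.90, threshold 0.95 − 0.10 = 0.85, one-sided α 0.20, power 0.80, LR share 75%, drop-off 15%.

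- n = (0.8416 + 0.8416)² × 0.90 × 0.10 / 0.05² = 102.0, so 102 LR patients, as stated.
- 102 / 0.75 / 0.85 = 160.0, so 160 enrolled, as stated.

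The point does not touch the sample size.

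**How a non-responder is scored.** Take an HR patient whose centrally read EoT-PET after nivolumab is not in complete metabolic response (CMR) but shows no progression.

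1. Not a relapse, so not an extended relapse under Section 2.3.
2. Not a death.
3. No other EFS event exists, because the list is closed in Section 2.6, the Discussion and Table 1.
4. The non-CMR result is linked to no endpoint, and starting new therapy is neither an event nor a censoring reason.

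The patient is event-free in EFS and in HR PFS.

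**Size per patient (no censoring).** HR patients: 160 × 0.25 = 40.

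- EFS: 1/160 = 0.6 points.
- HR PFS: 1/40 = 2.5 points.
- With the 15% drop-off taken out (160 × 0.85 = 136; 136 × 0.25 = 34): 1/136 = 0.7 points and 1/34 = 2.9 points.

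**Illustrative totals.** The article does not give the PET-2-positive count. Suppose that 5 to 15 of the 40 HR patients are PET-2-positive, that the historical 25% carries over, and that none of the non-responders later progresses or dies within 3 years:

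- Uncounted failures: 5 × 0.25 = 1.25 to 15 × 0.25 = 3.75.
- HR PFS: 1.25/40 = 3 points to 3.75/40 = 9 points.
- EFS: 1.25/160 = 0.8 points to 3.75/160 = 2.3 points.
- If all 40 were PET-2-positive: 10 patients, 25 points of HR PFS and 6 points of EFS.

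These are upper values under each assumed count, not estimates.

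**LR PFS, for the sensitivity analysis only.** With 102 patients and no censoring, the lower bound is p − 0.8416 × √(p(1 − p)/102).

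- 12 events: p = 0.8824, bound 85.55%, above 85%.
- 13 events: p = 0.8725, bound 84.48%, below 85%.
- If the true rate of being alive and disease-free is 85%, the binomial chance of 12 or fewer recorded events is 22%. It is 31–32% if 1% of patients have failures that go unrecorded, and 42–43% if 2% do. The 1% and 2% are assumptions.

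**The case against.** The article never says that non-response is a success; that follows from the list. It also uses the word relapse loosely. Table 1 describes the event for second treatment failure as progression during or after rescue, with extended relapse in brackets, so growth on treatment is probably already covered. A PFS that ignores non-response and new therapy is conventional, and the handling of new therapy is commonly left to an analysis plan, which is not shown. These arguments stand for the two PFS endpoints. They do not rescue EFS, which is defined by failure of the plan and whose list is expressly closed. An analysis plan that added events would contradict the article.

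A reader might infer that the primary endpoint is compromised, because non-responding LR patients count as chemotherapy-alone successes and one of them could reverse the conclusion. The documents do not support that:

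- LR status requires a negative PET-2 (Section 2.3), and in group 1a the EoT-PET is that same scan (Section 2.4).
- Only group 1b can be non-CMR at the end of treatment. A change there from Deauville 1–3 to 4–5 would plausibly be scored as recurrence, which already counts.
- The preferred primary analysis is per protocol (Section 2.6), so an LR patient given unplanned radiotherapy would plausibly be excluded rather than counted as a success.
- One-patient sensitivity at a decision boundary is true of any such rule and does not show that such a patient exists.
- The benchmark in Section 2.5 is a PFS figure. Adding non-CMR or new therapy to the primary definition would make the comparison unlike.

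A reader might also infer that the protocol expects 25% non-response in PET-2-positive patients here. That figure is historical, for CMT without nivolumab, and the article does not define non-response. The Discussion's statement that all patients finished planned treatment shows completion, not response, and so settles the matter neither way.

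**Conclusion.** The point holds for EFS. Its event list contradicts its stated purpose by leaving out persistent disease at the end of planned treatment and the start of unplanned lymphoma therapy. HR PFS has the same gap, but there the convention for PFS is a fair defence, so clearer wording and a sensitivity analysis are enough. For LR PFS the exposure is small. What remains is a mismatch between being alive and disease-free in Section 2.5 and progression or death in Section 2.6, which a sensitivity analysis can check.

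The size is about 0.6 points of EFS and 2.5 points of HR PFS per affected patient. This assumes 160 enrolled, an HR share of 25% and no censoring. The number of affected patients is unknown, so any total is illustrative. The endpoints mainly affected are secondary and descriptive. The change is still worth making, because the article gives EFS such weight and the bias runs in one direction.

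**What to change.** In Section 2.6, the Discussion and Table 1, add two events to EFS:

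- (a) Centrally confirmed failure to reach CMR at EoT-PET, dated at the scan. A LYRIC indeterminate response is to be resolved by the consensus review already described in Section 2.4 before it is scored.
- (b) The start of lymphoma therapy outside the planned pathway, dated at its start.

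State how (a) fits the existing limited-relapse rule: where a group 1b scan is classified as limited relapse and the patient enters the rescue pathway, the EoT-PET after rescue is the one that counts. Report the relapse-or-death-only version of EFS as a sensitivity analysis.

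Keep HR PFS and LR PFS as progression or death, but state that progression on or at the end of treatment counts as well as relapse. For each, add a sensitivity analysis that scores unplanned radiotherapy or other lymphoma therapy as an event. For LR PFS, also score non-CMR at EoT-PET in group 1b, so that the primary result can be checked against the wording of Section 2.5.

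The cost is a change of wording and derivation. Central EoT-PET reads and subsequent lymphoma treatment are already collected. Follow-up is still running, so the change can be dated and documented before analysis. The downside is a slightly lower reported EFS.
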